**Secondary endpoints**	
**Air temperature**	Definition: Ambient air temperature (in °C) Functional form: Continuous Measurement: DS1923 iButton Hygrochron heat and humidity measurement device
**Relative humidity**	Definition: Ratio of the amount of water vapor present in the air to the greatest amount possible at the same temperature (in %) Functional form: Continuous Measurement: DS1923 iButton Hygrochron heat and humidity measurement device
**Heat index**	Definition: Index that combines air temperature and relative humidity (using the formulae endorsed by the US National Oceanic and Atmospheric Administration (NOAA)) Functional form: Continuous Measurement: DS1923 iButton Hygrochron heat and humidity measurement device
**Indoor thermal comfort**	Definition: Current heat experience measured using heat strain score index. A score of < 13.5 indicates no or low heat strain, between 13.6–18 indicates potential for heat-induced illness, and > 18 indicates the onset of heat-induced illness Functional form: Categorical Measurement: Heat strain score index scale comprising 18 questions answered by individuals at the time of interview
**Systolic blood pressure**	Definition: Systolic blood pressure in mmHg Functional form: Continuous Measurement: Omron portable automated sphygmomanometers
**Diastolic blood pressure**	Definition: Diastolic blood pressure in mmHg Functional form: Continuous Measurement: Omron portable automated sphygmomanometers
**Body temperature**	Definition: Body temperature Functional form: Continuous Measurement: Inner ear thermometer
**Dehydration**	Definition: Loss of fluid greater than intake amount resulting in the body being unable to carry out its normal functions Functional form: Categorical Measurement: Urine hydration chart and question answered by individual
**Blood glucose (HbA1c)**	Definition: Average blood glucose measured over 3 months Functional form: Continuous Measurement: HemoCue® HbA1c 501 System to capture estimated average glucose (g/L)
**Sleep**	Definition: Number of hours slept and number of times the individual woke up Functional form: Count Measurement: Recall question answered by individual and smartwatch (in a subset of the cRCT population)
**Cognition**	Definition: The mental processes involved in gaining knowledge and comprehension Functional form: Continuous Measurement: Oxford Cognitive Screen (OCS)-Plus (assessing memory, language, visual-spatial ability, and executive functioning domains)

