**Depression**	Definition: Self-reported depression. Each response category of “not at all,” “several days,” “more than half the days,” and “nearly every day” is assigned a score of 0, 1, 2, and 3, respectively. The total score is calculated by adding together the scores for the nine questions. The final scores of 0–4, 5–9, 10–14, 15–19, and 20–27 are the ranges for none, mild, moderate, moderately severe and severe, respectively Functional form: Categorical Measurement: Patient Health Questionnaire 9 (PHQ-9) to screen and monitor depression
**Aggression**	Definition: Self-reported aggression. Responses to 12 items rated on a 5-point Likert scale are summed up as a measure of aggression. Higher scores indicate higher aggressive behavior. The module can generate four subscales: physical aggression (items 1, 4, 8), verbal aggression (items 2, 5, 9), anger (items 6, 10, 12), and hostility (items 3, 7, 11). The score for each scale is the sum of the ratings for its items Functional form: Categorical Measurement: Short Buss-Perry Aggression Questionnaire (BPAQ)
**Clinic utilization**	Definition: Clinic utilization in the past 3 months Functional form: Count Measurement: Recall question answered by individual
**Hospitalization**	Definition: Hospitalization in the past 12 months Functional form: Count Measurement: Recall question answered by individual
**Children’s educational attainment**	Definition: Highest school grade completed Functional form: Count Measurement: Question answered by household proxy respondent
**Household consumption expenditures**	Definition: Amount (XOF) spent on monthly expenditures Functional form: Continuous Measurement: Locally validated set of questions covering a comprehensive spectrum of expenditure categories in rural Burkina Faso, answered by household proxy respondent
**Food crop harvest**	Definition: Harvest weight per field surface (yield) in tons/m^2^ Functional form: Count measurement Measurement: Remote sensing (Sentinel-2 satellite, validated against weighed crops in 2019)
**Farmers’ movement**	Definition: Work pattern of the farmers during their fieldwork Functional form: Continuous Measurement: Portable GPS device
** Mosquito count**	Definition: Number of mosquitos in the light trap (collected at 0600 h) and aspirator (collected at 0900 h) over defined night cycles Functional form: Count Measurement: CDC miniature light trap, aspirator

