**Fig. 5 Fig5:**
[figure not shown]
Schedule of enrolment, intervention, and assessments

We are measuring the primary and secondary endpoints at varying times: every month during monthly home visits (including the primary endpoint, heart rate, and other individual health outcomes), continuously (home climate endpoints and smartwatch outcomes), and in two panel measurements over 1 year - the start of the trial and the end of the trial (long-term blood glucose — HbA1C).

Additionally, we are conducting three independent sub-studies using the cool roof trial infrastructure. First, we are quantifying the effect of cool roof use on mosquito abundance by counting mosquito abundance by species and gender in 120 households (60 with a cool roof versus 60 control homes) across ten villages at two weekly intervals over the rainy season. Second, we are quantifying the food crop harvest in each household’s fields and tracking household members’ work patterns using Global Positioning System (GPS) devices worn by the participants to compare farmer productivity in occupants of cool roof homes versus control homes. Third, we are quantifying the effect of cool roof use on food intake, psychosocial well-being, and gender-based violence.

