### Timeline

Our trial began on April 20, 2021. The end of COVID-19 restrictions for home visits coincided with the beginning of the rainy season in June 2021. Due to this short window, we could not collect baseline information from participants. Therefore, we conducted an intensive campaign before the rainy season to apply cool roofs on 300 homes between April 23, 2021, and June 4, 2021. Our 30 cool roof applicators traveled across 25 villages, coating 54 homes per week. Each home required no more than 1 week to coat, including the curing time between preparing the roof surface, primer application, first and second coat application. We verified the iButton data loggers, which measure indoor temperature in each home, were collecting data.

After encountering challenges caused by the COVID-19 pandemic, we faced intermittent delays in three key areas during our research project. First, we encountered difficulties maintaining participant retention due to early equipment malfunctions requiring replacement. Second, due to the rapidly changing on-the-ground security concerns, we had to modify participant questionnaires and make the corresponding ethical amendments. Third, ongoing security concerns in Burkina Faso, including the military’s restrictions on fieldworker movement and data collection, posed additional obstacles to our research progress.

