## Methods: data collection, management, and analysis

### Data collection plan

We are collecting trial data from a variety of sources for measuring health, indoor climate, economic, and behavioral outcomes (Table 2). Our primary outcome — heart rate — is collected monthly by trained field staff using an Omron portable automated sphygmomanometer. We present a complete list of secondary outcomes, including the associated instruments used for data collection in Table 2. Additionally, we are collecting continuous health indicators, including heart rate, sleep, and activity using a Withings Pulse HR or Garmin Vivosmart 5 smartwatch worn by a subset of participants.

We are collecting HbA1C blood samples - an indicator of long-term glucose control as two-panel measurements in the hottest months of 2021 and 2022, respectively, using the HemoCue® HbA1c 501 System. A qualified phlebotomist took 4 ml of whole blood by venipuncture for each participant. The phlebotomist labeled the collection tube with the participant's first and last name, and their household, individual and study identifying codes. Blood samples collected in different villages were stored in a refrigerator, and transfered to the laboratory within 48 h. Our laboratory technicians verified that HbA1c samples matched participants and recorded measurements systematically on examination forms according to protocols supplied by HemoCue®. Blood samples were subsequently disposed of in accordance with the laboratory's biological waste disposal procedure. We removed all identifiable information, except the individual identification code, prior to conducting data analysis.

We are collecting indoor temperature and humidity data using the DS1923-F5 iButton hygrochron temperature and humidity sensors. We are also conducting three independent sub-studies using the cool roof trial infrastructure that will be reported separately. First, we will investigate the effects of cool roofs on mosquito abundance, where light traps and aspirators are deployed during the rainy season to collect mosquito samples from a subset of households. Second, we will investigate the effects of cool roofs on farmer productivity, where GPS devices will record individual movement and remote sensing will provide data on crop harvest yield. Finally, we will investigate the effects of cool roofs on food consumption, psychosocial well-being, and gender-based violence from data collected during monthly home visits.

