### Statistical analysis

#### Analysis of monthly home visit data

The analysis for our primary outcome, heart rate, will be performed on the principle of intention-to-treat (ITT). We will use generalized linear mixed models (GLMM) to analyze the causal effect of cool roofs on our primary and secondary endpoints. In addition to the base-case estimations, without covariate controls, we will also estimate the intervention effect of cool roofs by adjusting for covariates to boost statistical efficiency. We will adjust for clustering of standard errors at the household level.

To estimate the intervention effect of cool roofs on heart rate, we will report the effect estimates comparing intervention and control arms based on the hypothesis that effects will be greatest during the hottest month of the year (April). We will additionally report effect estimates at monthly intervals of data collection, except for HbA1c (which is measured in two time points), because we hypothesize the intervention effect will vary based on outdoor weather conditions during the trial period; therefore, we will include an interaction term between the intervention and the month of trial. We will perform additional sub-analysis by selected variables where relevant (i.e., by season, gender, age group, time of the day (day/night), and roof type). We will explore the use of different imputation methods for missing values in the covariates. We will conduct sensitivity analysis, including repeating analyses accounting for individuals lost to follow-up. All data analyses will be performed using R software.

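### Hospitalisation recalled over 12 months, if asked monthly, reaches back before the roofs were coated and cannot yield the planned month-specific effects

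*Protocol article*

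**What the plan says.** Table 2 of the protocol article lists two health-care use endpoints as recall counts: "Definition: Hospitalization in the past 12 months" and "Definition: Clinic utilization in the past 3 months". Neither definition limits the look-back to time since coating. The text after Fig. 5 puts heart rate and the other individual health outcomes at the monthly home visits, and the abstract describes 2 years of monthly visits.

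*Analysis of monthly home visit data* states: "We will additionally report effect estimates at monthly intervals of data collection, except for HbA1c (which is measured in two time points". It adds an interaction between intervention and trial month, because the effect is expected to vary with outdoor weather.

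Under *Timeline*, the campaign was to "apply cool roofs on 300 homes between April 23, 2021, and June 4, 2021". The same section says that "The end of COVID-19 restrictions for home visits coincided with the beginning of the rainy season in June 2021" and that no baseline data were obtained from participants. *Trial status* gives 30 June 2023 as the end of data collection.

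For HbA1c, Table 2 has "Definition: Average blood glucose measured over 3 months". The text after Fig. 5 says it is taken "in two panel measurements over 1 year - the start of the trial and the end of the trial", while *Data collection plan* says "two-panel measurements in the hottest months of 2021 and 2022".

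**The concern.** A question about the past 12 months, asked a few weeks after coating, is answered mostly from the time before coating, when the arms do not differ in treatment. Until about 12 months after coating, every answer mixes untreated with treated time. The intervention contrast is pulled toward the null, most in the first year.

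A second fault remains even when the whole window lies after coating. The plan wants effects by month because it expects them to follow the weather. A 12-month window covers every season, so an estimate labelled April describes the preceding year. The 3-month clinic-use window has this fault to a lesser degree.

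For HbA1c, the article's statements about when the two panels were taken, and whether the first is a baseline, do not fit together. Its reported effect depends on the role given to the 2021 panel.

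**Working it through.** The plan gives no rate, power or effect figure for these endpoints, so there is none of its own to reproduce. The check is date arithmetic.

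**Inputs from the article.** Windows of 12 and 3 months (Table 2); coating 23 April to 4 June 2021 (*Timeline*); monthly visits (abstract, text after Fig. 5); data collection to 30 June 2023 (*Trial status*).

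**Assumptions.** Both questions asked at every visit; first visit mid-June to mid-August 2021, because the article gives no date but says home-visit restrictions ended about June 2021; event rates constant over time apart from the intervention effect; true rate ratio 0.80, for illustration.

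**Hand check.** At a visit k months after coating, a w-month window has a pre-coating share of max(0, (w − k)/w). For w = 12, the shares at k = 1 to 12 are 11/12, 10/12, …, 0. Their mean is 66/144 = 46% over the first 12 visits and 66/288 = 23% over 24.

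**By calendar date, hospitalisation** (mean share over the first 12 visits / over all visits):

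| First visit (number of visits) | Coated 23 April | Coated 14 May | Coated 4 June |
|---|---|---|---|
| Mid-June 2021 (25) | 40.1% / 19.2% | 45.3% / 21.8% | 51.1% / 24.5% |
| Mid-July 2021 (24) | 32.9% / 16.5% | 37.7% / 18.9% | 43.0% / 21.5% |
| Mid-August 2021 (23) | 26.5% / 13.8% | 30.8% / 16.1% | 35.6% / 18.6% |

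Between 9 and 12 visits reach back before coating. The share is 2-14% in April 2022 and 0% in April 2023.

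**Dilution.** With pre-coating share s, the apparent rate ratio is s + (1 − s) × 0.80.
- First 12 visits: 0.265 + 0.735 × 0.80 = 0.853, to 0.511 + 0.489 × 0.80 = 0.902.
- All visits: 0.138 + 0.862 × 0.80 = 0.828, to 0.245 + 0.755 × 0.80 = 0.849.

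**Clinic use.** By the hand formula with w = 3, the share over 24 visits is (2/3 + 1/3 + 0)/24 = 4%. By calendar date, 0 to 3 visits reach back and the share over all visits is 0-6.5%, so 0.80 appears as 0.80-0.81. In the least favourable case (first visit mid-June, home coated 4 June), the share over the first 12 visits is 13.6%, giving 0.83. From about September 2021 it is zero.

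**Month-specific effects.** Consecutive 12-month windows share 11/12 of their time. An effect confined to one month carries a weight of 1/12 in any estimate containing it and stays there for 12 visits. For 3-month windows, the overlap is 2/3, the weight 1/3 and the persistence three visits.

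**Overlap alone.** A simulation used 600 people per arm, assumed monthly rates of 0.010 and 0.008, 36 post-coating months and 1,000 repeats. The mean rate ratio was 0.807 with rolling 12-month windows and 0.805 with monthly counts (SD 0.086 and 0.079). With 12 pre-coating and 24 post-coating months, it was 0.852.

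**HbA1c.** Taking 3 months as 91 days, a sample on 30 April 2021 has 92-100% of its window before coating, one on 31 May 58-100%, and one on 30 June 25-71%. A sample in March to May 2022 has none.

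**The case against.** The strongest objection is that monthly asking is nowhere stated. The article says endpoints are measured at varying times, and the schedule is in Fig. 5, which is not shown. The monthly-reporting sentence cannot be literal for every endpoint, since Table 2 includes school grade completed and satellite crop yield. Had hospitalisation been asked only in June 2022 and June 2023, the pre-coating share would be zero and the windows would not overlap. This stands as a condition on the point. It does not remove it, because the text places individual health outcomes at monthly visits and exempts only HbA1c from monthly estimates.

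Three stronger readings are tempting, and the document does not support them.

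- A reader might infer that overlapping windows themselves dilute the effect or inflate it by repeated counting. Overlap counts an admission up to 12 times, but in both arms alike, and the simulated ratio hardly moves. The serial correlation is addressed by the planned household-level clustering of standard errors.
- A reader might infer that clinic use is diluted as hospitalisation is. Pooled over visits, the change is at most from 0.80 to 0.81.
- A reader might infer that the HbA1c effect is halved. That needs the two panels averaged with equal weight as outcomes, which the article never says. HbA1c is a biomarker, and its two windows are about a year apart. A first panel drawn largely before coating would be close to a baseline.

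The HbA1c conflict is also narrower than it may look. Panels in 2021 and 2022 fit a span of 1 year, and the lack of baseline data is compatible with a first panel drawn after coating. What cannot be squared is a second panel at the end of the trial with one in the hottest months of 2022, when data collection ran to 30 June 2023.

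**Conclusion.** The point holds for hospitalisation, conditional on monthly asking. First-year estimates would be attenuated from 0.80 to about 0.85-0.90 and estimates pooled over all visits to about 0.83-0.85. These figures rest on the assumed first-visit range and constant underlying rates; a different true ratio shrinks toward 1 by the same proportion. The failure to isolate a month does not depend on coating dates and applies to clinic use too.

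For HbA1c, what is established is a conflict between timing statements and an undefined role for the 2021 panel, not a bias of known size. If that panel was drawn in the hot season (March to May under *Setting*), most of its window precedes coating, and the statement that no baseline was collected needs qualifying.

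These are secondary endpoints and heart rate is untouched. The matter should be corrected before analysis but does not threaten the trial's main conclusion.

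**What to change.** **Hospitalisation.** Use only windows that lie wholly after coating and do not overlap: the visits nearest 12 and 24 months after the stratum's coating date, with the same date applied to its control homes. Taking the latest coating date in the stratum, and the first visit on or after 12 months, keeps the first window clear of uncoated time. The second window fits narrowly: 24 months after the last coating is 4 June 2023, 26 days before collection closed, so state a tolerance of a few days.

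**Clinic use.** Use non-overlapping 3-month windows, that is, every third visit from 3 months after coating (24/3 = 8 windows over 24 months).

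**Both.** Drop the month-specific estimates and the intervention-by-month interaction. State how often each question was asked; if the schedule already has hospitalisation yearly and clinic use quarterly, only the wording on monthly estimates needs to change.

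**HbA1c.** Reconcile the text after Fig. 5, *Data collection plan* and *Timeline* on when the panels were taken and whether the first is a baseline. Name the 2022 panel as the outcome, and do not pool it with the 2021 panel.

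**Cost.** Wording only, applied to data already collected, plus coating dates by stratum, which the article does not give. Fewer visits contribute: two per participant for hospitalisation instead of 23-25. Two windows of 12 months still span nearly all of the time after coating, so the main loss is from participants who miss the chosen visits.

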**Fig. 5 Fig5:**
[figure not shown]
Schedule of enrolment, intervention, and assessments

We are measuring the primary and secondary endpoints at varying times: every month during monthly home visits (including the primary endpoint, heart rate, and other individual health outcomes), continuously (home climate endpoints and smartwatch outcomes), and in two panel measurements over 1 year - the start of the trial and the end of the trial (long-term blood glucose — HbA1C).

Additionally, we are conducting three independent sub-studies using the cool roof trial infrastructure. First, we are quantifying the effect of cool roof use on mosquito abundance by counting mosquito abundance by species and gender in 120 households (60 with a cool roof versus 60 control homes) across ten villages at two weekly intervals over the rainy season. Second, we are quantifying the food crop harvest in each household’s fields and tracking household members’ work patterns using Global Positioning System (GPS) devices worn by the participants to compare farmer productivity in occupants of cool roof homes versus control homes. Third, we are quantifying the effect of cool roof use on food intake, psychosocial well-being, and gender-based violence.

### Timeline

Our trial began on April 20, 2021. The end of COVID-19 restrictions for home visits coincided with the beginning of the rainy season in June 2021. Due to this short window, we could not collect baseline information from participants. Therefore, we conducted an intensive campaign before the rainy season to apply cool roofs on 300 homes between April 23, 2021, and June 4, 2021. Our 30 cool roof applicators traveled across 25 villages, coating 54 homes per week. Each home required no more than 1 week to coat, including the curing time between preparing the roof surface, primer application, first and second coat application. We verified the iButton data loggers, which measure indoor temperature in each home, were collecting data.

After encountering challenges caused by the COVID-19 pandemic, we faced intermittent delays in three key areas during our research project. First, we encountered difficulties maintaining participant retention due to early equipment malfunctions requiring replacement. Second, due to the rapidly changing on-the-ground security concerns, we had to modify participant questionnaires and make the corresponding ethical amendments. Third, ongoing security concerns in Burkina Faso, including the military’s restrictions on fieldworker movement and data collection, posed additional obstacles to our research progress.

We obtained funding for our cRCT from the German Research Foundation (Deutsch Forschungsgemeinschaft, DFG) to execute the study in Nouna, Burkina Faso. Soon after securing funding, the security situation in Burkina Faso deteriorated, particularly in our study region. The primary security concerns included fear of attacks on villagers, including our participants, from Islamic insurgency groups. From this point onwards, we constantly interacted with our Burkinabe government partners (the National Institute of Public Health) and our community partners (CSRN and the community advisory board) to consider the advantages and disadvantages of implementing and continuing the study. We prepared contingency plans to relocate our cRCT to a more secure location, including to another country — Kenya. In the event of relocation, we did not want to publish a trial protocol that inaccurately stated the country or community of a cRCT because future reviewers of our trial publications would find it confusing and incorrect that we had published a protocol in Nouna Burkina Faso, but were attempting to publish the results of a potentially relocated study in Kenya. Through our ongoing safety and security monitoring process, we ensured participant safety and successfully executed our cRCT in the originally intended location of Nouna, Burkina Faso. For this reason, we are submitting this study protocol post-participant recruitment but before the last data collection on June 30, 2023.

